### 6.3 CETUXIMAB

#### Availability/Product Description

Cetuximab is an anti-EGFR receptor humane-to-murine chimeric antibody. Cetuximab is expressed in SP2/0 myeloma cell line, grown in large scale cell culture bioreactors and purified to a high level purity using several purification steps including protein A chromatography, ion exchange chromatography, low pH treatment and nonofiltration. Cetuximab is not known to be a vesicant.

The product is formulated to 2 mg protein/mL with phosphate buffered saline, pH 7.2  $\pm$  0.2 and aseptically filled into sterile glass vials, 100 mg per 50 cc vial, and stored as a liquid at 2 to 8 °C. Each vial contains the following active and inactive ingredients per 1.0 mL: 2 mg of cetuximab, 145 nmol/L sodium chloride, and 10 mmol/L sodium phosphate.

Cetuximab is obtained in single-use, ready-to-use 50-mL vials containing 2 mg/mL of product. Cetuximab must be stored under refrigeration at +2°C to +8°C (+36°F to +46°F). DO NOT FREEZE CETUXIMAB. Commercially available cetuximab will be used in this protocol and charged to patient's insurance company.

#### Drug Administration

Cetuximab requires no dilution. Patients will receive weekly cetuximab intravenous infusions via either gravity drip, infusion pump, or syringe pump with in-line filtration. Cetuximab should not be mixed with or diluted with other drugs or solutions for infusion. The dose and volume of the study drug to be infused are dependent upon the patient's BSA. The infusion rate must never exceed 10 mg/minute (5 mL/minute).

Appropriate mask, protective clothing, eye protection, gloves and Class II vertical-laminar-airflow safety cabinets are recommended during preparation and handling. Opened vials must be disposed of as chemotherapy or biohazardous waste provided documented procedures for destruction are in place.

Patients no longer require a 'test dose' prior to the loading dose of Cetuximab.

For the first treatment with cetuximab, patients will be premedicated with 50 mg IV of Benadryl 30-60 minutes prior to receiving 400mg/m^2 of Cetuximab. Premedication may be administered prior to subsequent doses, but at the Investigator's discretion, the dose of diphenhydramine (or similar agent) may be reduced.

The initial dose of cetuximab is 400 mg/m^2 intravenously administered over 120 minutes, followed by weekly infusions at 250 mg/m^2 IV over 60 minutes. **The infusion rate of cetuximab must never exceed 10 mg/minute (5 mL/min).**

Vital signs will be obtained per institute standards, and as necessary to monitor for Cetuximab-related adverse events during and post infusion.

**CAUTION:** Hypersensitivity reactions, including severe reactions, may occur during or following cetuximab administration. Most hypersensitivity reactions occur with the first infusion of cetuximab, but some patients' first hypersensitivity reactions have been reported following subsequent doses (a severe reaction occurred in one patient following the 8th dose). A nurse must be present in the immediate treatment area throughout the infusion and observation period. A physician must be in close proximity to the patient treatment area. **Patients should be instructed to report any delayed reactions to the Investigator immediately.**

Severe hypersensitivity reactions, characterized by airway obstruction (bronchospasm, stridor and hoarseness, urticaria, and/or hypotension, require immediate interruption of cetuximab infusion and permanent discontinuation from further treatment with cetuximab. Appropriate medical therapy including epinephrine, corticosteroids, diphenhydramine, bronchodilators, and oxygen should be available for use in the treatment of such reactions. Subjects should be carefully observed until the complete resolution of all signs and symptoms.

Mild to moderate (Grade 1 or 2) hypersensitivity reactions are managed by slowing the infusion rate for cetuximab and by employing prophylactic use of antihistamine medications for subsequent doses. For mild or moderate hypersensitivity reactions manifesting only as delayed drug fever, maintain the cetuximab dose and infusion rate. Administration of acetaminophen or a non-steroidal anti-inflammatory drug (NSAID) may be administered prior to subsequent cetuximab infusions, if not otherwise contraindicated in subjects.

Once a cetuximab infusion rate has been decreased due to a hypersensitivity reaction, it will remain decreased for all subsequent infusions. If a subject has a second hypersensitivity reaction with the slower infusion rate, the infusion should be stopped and the subject should receive no further cetuximab treatment.

Once a cetuximab infusion rate has been decreased due to an allergic/hypersensitivity reaction, it will remain decreased for all subsequent infusions. If the patient has a second allergic/hypersensitivity reaction with the slower infusion rate, the infusion should be stopped, and the patient should receive no further cetuximab treatment. If a patient experiences a Grade 3 or 4 allergic/hypersensitivity reaction at any time, the patient should receive no further cetuximab treatment. If there is any question as to whether an observed reaction is an allergic/hypersensitivity reaction of Grades 1 - 4, the overall principal investigator should be contacted immediately to discuss and grade the reaction.

Toxicities in Humans

The incidence of the most significant or common adverse events occurring in single-agent cetuximab trials and by relationship to cetuximab, are presented in the following table:

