## 7.2 CETUXIMAB DOSE MODIFICATIONS

### 7.2.1 Management of Infusion Reactions

Infusion reactions should be graded according to allergic reaction/hypersensitivity. Caution must be exercised with every cetuximab infusion, as there were patients who experienced their first severe infusion reaction during later infusions. Severe infusion reactions require the immediate interruption of cetuximab therapy and permanent discontinuation from further treatment. Appropriate medical therapy including epinephrine, corticosteroids, intravenous antihistamines, bronchodilators, and oxygen should be available for use in the treatment of such reactions. Patients should be carefully observed until the complete resolution of all signs and symptoms. In clinical trials, mild to moderate infusion reactions were managed by slowing the infusion rate of cetuximab and by continued use of antihistamine premedications (eg, diphenhydramine) in subsequent doses. If the patient experiences a mild or moderate (Grade 1 or 2) infusion reaction, the **infusion rate** should be permanently reduced by 50%. For grade 1 or 2 reactions manifesting only as delayed drug fever, maintain the cetuximab dose and infusion rate. Consideration should be given to administration of acetaminophen or a nonsteroidal anti-inflammatory drug (NSAID)

prior to the subsequent cetuximab infusion if not contraindicated in subjects. Dose and schedule of these agents is entirely at the investigator's discretion.

Cetuximab should be immediately and permanently discontinued in patients who experience severe (Grade 3 or 4) infusion reactions and will need to be removed from the trial.

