#### 7.2.2 Treatment of Isolated Drug Fever

In the event of isolated drug fever, the investigator must use clinical judgment to determine if the fever is related to the study drug or to an infectious etiology. If a patient experiences isolated drug fever, for the next dose, pre treat with acetaminophen or non-steroidal anti-inflammatory agent (investigator discretion), repeat antipyretic dose 6 and 12 hours after cetuximab infusion. The infusion rate will remain unchanged for future doses. If a patient experiences recurrent isolated drug fever following premedication and post-dosing with an appropriate antipyretic, the infusion rate for subsequent dosing should be 50% of previous rate. If fever recurs following infusion rate change, the investigator should assess the patient's level of discomfort with the event and use clinical judgment to determine if the patient should receive further cetuximab.

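### Sections 6.3 and 7.2 of the protocol give incompatible instructions on continuing cetuximab when drug fever occurs at an already reduced infusion rate, and 7.2.1 omits the repeat-reaction stop rule

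*Protocol*

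**What the plan says.** Three parts of the protocol govern mild cetuximab reactions.

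- **Section 6.3, Drug Administration.** Grade 1-2 hypersensitivity reactions are handled by slowing the infusion. Fever is named as one form such a reaction can take: "For mild or moderate hypersensitivity reactions manifesting only as delayed drug fever, maintain the cetuximab dose and infusion rate". Once the rate has been lowered for a hypersensitivity reaction it stays lowered. The stop rule follows: "If a subject has a second hypersensitivity reaction with the slower infusion rate, the infusion should be stopped", and cetuximab is not given again. It appears in two consecutive paragraphs, neither with a carve-out for fever.
- **Section 7.2.1, Management of Infusion Reactions.** It covers the same class of event: "Infusion reactions should be graded according to allergic reaction/hypersensitivity". After a grade 1-2 reaction the infusion rate "should be permanently reduced by 50" percent. Fever is again separated out: "For grade 1 or 2 reactions manifesting only as delayed drug fever, maintain the cetuximab dose and infusion rate". Grade 3-4 reactions end cetuximab. A second grade 1-2 reaction is not mentioned.
- **Section 7.2.2, Treatment of Isolated Drug Fever.** After a first fever, antipyretics are given and the rate is kept. If fever recurs despite them, "the infusion rate for subsequent dosing should be 50% of previous rate". If it recurs again, the investigator is to weigh the patient's discomfort and "use clinical judgment to determine if the patient should receive further cetuximab".

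Section 5.1 refers sites to Sections 6 and 7 together for expected adverse events and dose modifications. Section 11 ties toxicity withdrawals to Section 7.

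**The concern.** Whether a patient goes on receiving cetuximab should not depend on which section the site opens. The primary objective is the tolerability and MTD of ZD6474, cetuximab and irinotecan together, so a rule that removes one of the three drugs determines who remains on the combination being assessed. It is also a patient-safety rule: a site working only from Section 7 would not see the stop instruction in 6.3.

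The decision can fall early. Cetuximab is weekly, so fever on day 1, again on day 8 despite antipyretics, and again on day 15 at half rate forces a choice before the day 22 infusion. That lies inside the DLT window of 28 days (dose level 1) or 35 days (levels 2-4), during which Section 7 expects patients to stay on their assigned doses.

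**Working it through.** The protocol gives no figure to reproduce here, so the check sets the rules side by side for each event.

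| Event | 6.3 | 7.2.1 | 7.2.2 | Result |
|---|---|---|---|---|
| First isolated drug fever, rate not yet reduced | Keep dose and rate | Keep dose and rate | Antipyretics, keep rate | Agree |
| Fever recurs despite antipyretics, full rate | No separate step | No separate step | Halve rate | 7.2.2 adds a step |
| Fever again at the halved rate | Read literally, stop for good | No separate step | Investigator's judgment | **Conflict** |
| First fever-only reaction after the rate was cut for another mild reaction | Read literally, stop for good | Keep dose and rate | Antipyretics, keep rate | **Conflict** |
| Second non-fever grade 1-2 reaction at the reduced rate | Stop for good | Silent | Does not apply | Omission in 7.2.1 |
| Grade 3-4 reaction | Stop for good | Stop for good | Does not apply | Agree |

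The first conflict rests on two steps. Section 6.3 words delayed drug fever as a manifestation of a hypersensitivity reaction, and its stop rule counts hypersensitivity reactions without excluding fever. The second conflict is more direct: the rate was lowered for a hypersensitivity reaction, exactly as 6.3 requires, and the fever is then the second reaction at the slower rate.

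**What can be said about size.** The inputs come from the single-agent cetuximab table in 6.3 (n = 281).

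- Related fever: 75 of all grades, 0 of grade 3-4, so all 75 were grade 1-2. 75/281 = 26.7%.
- Allergic reaction: 24 of all grades, 8 of grade 3-4. Grade 1-2: 24 − 8 = 16, and 16/281 = 5.7%.
- Related allergic reaction: 18 of all grades, 8 of grade 3-4. Grade 1-2: 18 − 8 = 10, and 10/281 = 3.6%.

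The 26.7% bounds entry at the first row of the table, where the sections agree. The first conflict needs a third fever, at half rate, after antipyretics have failed. The second needs a mild reaction and then a fever; the 5.7% indicates how many could start on that route, if the allergic-reaction row captures mild infusion reactions. The documents give no rate for any later step, so the share of patients reaching either conflict cannot be calculated.

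**The case against.** The strongest defence is that the sections can be read in harmony. The stop rule in 6.3 follows a sentence about a rate lowered for a hypersensitivity reaction. Within 6.3 a fever-only reaction never lowers the rate, so the first conflict appears only when the rate cut is imported from 7.2.2. Section 7.2.2 is the specific, separately headed rule for isolated fever and could be taken to prevail, and the instruction in 6.3 to keep dose and rate for fever could be taken as an implied exception. Finally, 6.3 sends doubtful cases to the overall principal investigator.

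Part of this stands: the first conflict does depend on how 6.3 is read. But no text gives 7.2.2 priority, the stop rule is not made subject to the fever sentence, and Section 5.1 invokes both sections. The referral covers doubt about whether an event is a hypersensitivity reaction and its grade; it does not say which stopping rule applies to a fever that 6.3 already words as such a reaction. The second conflict needs no rate cut from 7.2.2.

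Two stronger readings are tempting and fail:

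- *That one repeat event receives three outcomes, with 7.2.1 merely slowing the infusion.* The halving in 7.2.1 is its response to a grade 1-2 reaction in general. It says nothing about a repeat, and it does not slow the infusion for fever alone. Section 7.2.2 covers isolated fever only. A repeat non-fever reaction therefore has one stated rule, in 6.3.
- *That keeping the rate (6.3, 7.2.1) contradicts halving it (7.2.2).* Section 7.2.2 also keeps the rate after a first fever. Halving is a later step that the other two do not address.

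**Conclusion.** The point holds in limited form. Sections 6.3 and 7.2.2 conflict for drug fever recurring at a halved rate, and 6.3 conflicts with 7.2.1 and 7.2.2 for a fever-only reaction after the rate was cut for another mild reaction. Both rest on taking 6.3 at its word that delayed drug fever is a hypersensitivity reaction. Separately, 7.2.1 omits the repeat-reaction rule; that is a gap, not an opposing instruction.

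The size is unknown. A reader might infer from the table that about a quarter of patients are affected. The documents do not support this: the figure counts any related fever under cetuximab alone, at a step where the sections agree.

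A reader might also infer that DLT counts or the MTD are compromised. That is not shown. Fever without neutropenia is a DLT only at grade 3 or higher for more than a week, and the table has no related grade 3-4 fever. What is shown is that continuation of cetuximab, and hence exposure to the triplet, could differ between sites for the same clinical course.

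**What to change.** Amend 6.3, 7.2.1 and 7.2.2 so that they express one rule. The amendment should:

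- state whether isolated drug fever counts toward the second-reaction stop rule, both when the rate was cut for fever and when it was cut for another mild reaction;
- state the rule for a repeat grade 1-2 reaction in 7.2.1, or cross-refer there to 6.3;
- say which section governs if the wording differs.

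Which clinical rule applies is for the sponsor to decide. The cost is amendment wording, with no change to data collection or sample size.

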**Adverse Events in Single-Agent Cetuximab Trials\***  
**(n = 281, as of November 30, 2002)**

|                          | All Adverse Events |      |              |     | Related Adverse Events** |      |              |       |
|--------------------------|--------------------|------|--------------|-----|--------------------------|------|--------------|-------|
|                          | Grades 1 - 4       |      | Grades 3 & 4 |     | Grades 1 - 4             |      | Grades 3 & 4 |       |
|                          | N                  | (%)  | N            | (%) | N                        | (%)  | N            | (%)   |
| Asthenia                 | 127                | (45) | 21           | (7) | 71                       | (25) | 8            | (3)   |
| Nausea                   | 76                 | (27) | 3            | (1) | 38                       | (14) | 0            | (0)   |
| Rash                     | 87                 | (31) | 8            | (3) | 86                       | (31) | 6            | (2)   |
| Acne                     | 104                | (37) | 20           | (7) | 104                      | (37) | 20           | (7)   |
| Diarrhea                 | 53                 | (19) | 3            | (1) | 26                       | (9)  | 3            | (1)   |
| Vomiting                 | 66                 | (24) | 9            | (3) | 26                       | (9)  | 2            | (1)   |
| Fever                    | 99                 | (35) | 2            | (1) | 75                       | (27) | 0            | (0)   |
| Anorexia                 | 53                 | (19) | 8            | (3) | 13                       | (5)  | 1            | (< 1) |
| Weight Loss              | 24                 | (9)  | 0            | (0) | 3                        | (1)  | 0            | (0)   |
| Dry Skin                 | 35                 | (13) | 2            | (1) | 33                       | (12) | 2            | (1)   |
| Dyspnea                  | 51                 | (18) | 20           | (7) | 11                       | (4)  | 3            | (1)   |
| Mucous Membrane Disorder | 17                 | (6)  | 3            | (1) | 9                        | (3)  | 1            | (< 1) |
| Headache                 | 64                 | (23) | 3            | (1) | 40                       | (14) | 2            | (1)   |
| Stomatitis               | 26                 | (9)  | 7            | (3) | 13                       | (5)  | 0            | (0)   |
| Chills                   | 13                 | (5)  | 2            | (1) | 0                        | (0)  | 0            | (0)   |
| Pruritus                 | 25                 | (9)  | 2            | (1) | 21                       | (8)  | 1            | (< 1) |
| Nail Disorder            | 21                 | (8)  | 0            | (0) | 18                       | (6)  | 0            | (0)   |
| Allergic Reaction        | 24                 | (9)  | 8            | (3) | 18                       | (6)  | 8            | (3)   |
| Anaphylactoid Reaction   | 4                  | (1)  | 4            | (1) | 4                        | (1)  | 4            | (1)   |

\* Data from 281 patients enrolled in 12 trials receiving single-agent cetuximab. All adverse events reported by investigator and by relationship to cetuximab.

\*\* Possible, probably or definite relationship to cetuximab as reported by investigator.

The most common adverse event associated with cetuximab administration is acne-like rash. Acne-like rash usually occurs on the face, upper chest, and back, but occasionally extends to the extremities and is characterized by multiple follicular-or pustular-appearing lesions characterized histologically as lymphocytic perifolliculitis or suppurative superficial folliculitis in patients with metastatic carcinoma. The onset of the rash is generally within the first 3 weeks of therapy. In patients who received cetuximab at doses less than 100 mg/m^2, acne-like rash was reported infrequently and was restricted to Grades 1 or 2. A number of therapeutic interventions have been attempted, including oral and topical antibiotics, topical steroids, and rarely, oral steroids. The value of these measures is unknown since definitive clinical trials have

not been performed. The etiology of the acne-like skin rash is believed to be the result of cetuximab binding to EGFR in the epidermis.

An uncommon adverse event reported is a nail disorder characterized as paronychia inflammation with associated swelling of the lateral nail folds of the toes and fingers. The most commonly affected digits are the great toes and thumbs. According to Investigators, the nail disorder may persist for up to 3 months after discontinuation of cetuximab. Preliminary analysis in patients treated at the doses to be administered in this trial (400 mg/m^2 initial dose, followed by 250 mg/m^2 weekly) revealed that incidence of nail disorder is greater in patients who received > 6 cetuximab infusions (~10%) compared with patients treated with ≤ 6 infusions (~3%).

As cetuximab is a protein, the potential exists for allergic reaction to occur during or following cetuximab administration. In clinical trials, severe hypersensitivity reactions (including allergic and anaphylactic reactions), characterized by the rapid onset of airway obstruction (bronchospasm, stridor, hoarseness), urticaria, and/or hypotension, have been observed in approximately 3% of patients treated with cetuximab. The large majority of these severe reactions occurred with the first infusion of cetuximab and were observed during or within one hour of the completion of dosing.

## **7 DOSE and SCHEDULE MODIFICATIONS**

This Phase I study is intended to establish the maximum tolerated dose (MTD) of the combination of cetuximab, ZD6474 and irinotecan. DLTs (defined as within the first 28 days of treatment in dose level 1 and first 35 days in dose levels 2-4) will include: grade IV hematological toxicity > 7 days; fever and neutropenia; grade III diarrhea leading to hospitalization or lasting > 48 hours despite aggressive anti-diarrheal medication; grade IV diarrhea despite aggressive anti-diarrheal medication; grade IV vomiting despite optimal antiemetics; or grade III or higher nonhematological toxicity (excluding nausea, vomiting, diarrhea, or alopecia) lasting > 1 week; grade 4 skin toxicity; grade 3 or greater cardiac toxicities; or death. If patients in dose levels 2-4 who have a DLT in the first 14 days (prior to initiation of irinotecan), the patient will not be counted towards the DLTs of that cohort and an additional patient will be substituted. For example, if one of the first 3 patients in dose level 3 have a DLT, that patient will not be calculated into the DLT tabulation for ZD6474, cetuximab and irinotecan and an additional patient will be substituted in that spot. If this scenario occurs twice, the study will be held and the study team will reevaluate the ZD6474 / cetuximab toxicities.

Patients should remain on the assigned doses of therapy throughout the period of assessment of DLTs (first 28 days in dose level 1 and 35 days in dose levels 2-4) unless a DLT is observed or the patient is withdrawn from study for other reasons. The following guidelines for dosing delay and/or dose modifications apply to patients who either experience a DLT during the first 28 days (dose level 1) or 35 days (dose levels 2-4) OR develop treatment-related toxicities after that period of assessment.

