Gastrointestinal events (77.3%, 59.5%, 41.5%), and skin events (72.7%, 64.3%, 41.5%) were more common in the ZD6474-containing arms. For all arms, the majority of these events were common toxicity criteria (CTC) grade 1 and 2; however CTC grade 3/4 events were more prominent in the ZD6474 300 mg arm. Cardiac disorders occurred more frequently in ZD6474-containing arms (15.9%, 14.3%, 2.4%). The majority were CTC grade 1/2 and included a variety of terms, none ventricular. The frequency of respiratory events (50.0%, 57.1%, 46.3%) was similar in all arms. Neutropenia (31.8%, 26.2%, 19.5%) and related terms were more common in ZD6474-containing arms, but this did not result in an increase in infection. There was little difference in frequency of other hematologic events.

Approximately 10% of patients receiving ZD6474 developed an AE of hypertension. The majority of events were CTC grade 1 or 2, and no events were CTC grade 4. There were no serious adverse events (SAEs) of hypertension. The maximum median rise in both systolic and diastolic blood pressure was approximately 8 mm Hg in patients who received ZD6474 300 mg, and approximately 4 mm Hg in patients who received ZD6474 100 mg.

There were 12 subjects with confirmed QTc prolongation in Study ZD6474IL/0003. Of these, 6 occurred in the first 28 days, and 2 in the following 28 days. The remaining 4 occurred sporadically, with the longest time to occurrence 323 days. There were 3 events of CTC grade 1 reversible dizziness in subjects with a confirmed QTc prolongation occurring within the first 4 weeks. Subjects with dizziness had other events that might have caused dizziness and the events were not well correlated in time with the actual QTc prolongation. There were no other potentially relevant adverse events in subjects with confirmed QTc prolongation within the first 4 weeks, and no relevant adverse events in subjects whose first confirmed QTc prolongation occurred more than 4 weeks after randomization.

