### 7.1.3 Management of Patients With QTc Prolongation

For a single QTc value of  $\geq 550$  msec or an increase of  $\geq 100$  msec from baseline, ZD6474 must be withheld. ECGs and electrolytes should be followed 3 times a week until QTc falls below 480 msec or baseline, whichever is higher. ZD6474 treatment may be resumed at a lower dose after the QTc recovers to  $< 480$  msec or baseline. For a QTc interval  $\geq 500$  msec, but  $< 550$  msec, or an increase of  $\geq 60$  msec but  $< 100$  msec from baseline QTc to a QTc value  $\geq 480$  msec, ZD6474 may be continued but a repeat ECG (in triplicate) must be obtained within 48 hours. If QTc prolongation is confirmed, ZD6474 should be withheld. ECGs and electrolytes should be checked 3 times a week until QTc falls below 480 msec or baseline, whichever is higher. ZD6474 treatment may be resumed at a lower dose, as outlined in section 7.1.1 after the QTc recovers to  $< 480$  msec or baseline. If the patient does not meet the criteria for QTc prolongation at the repeat ECG, then the patient should continue treatment and resume the ECG schedule as outlined in the Study Plan.

If ZD6474 is restarted after the QTc prolongation has resolved, ECGs should be performed 1, 2, 4, 8, 12 weeks and then every 3 months after treatment is restarted. If ZD6474 must be withheld for  $> 3$  weeks to allow for QTc prolongation to recover to  $< 480$  msec or baseline, the patient will be withdrawn from study. If QTc prolongation recurs after the dose reduction as detailed, the patient must permanently discontinue treatment with study medication.

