#### 7.3.2 Hematological toxicities (excluding febrile neutropenia)

Dose reductions will be determined based on blood counts on the day irinotecan should be resumed (unless patient had documentation of grade 4 neutropenia OR had

an episode of febrile neutropenia defined as ANC < 1000 and temperature at least 38.5°C). No dose reductions will be made for anemia.

| Hematological Toxicity
(on day of start of scheduled dose of
irinotecan unless febrile neutropenia
or grade 4 neutropenia) | Action                                                                           | Resumption of therapy                                                                                         |
|-----------------------------------------------------------------------------------------------------------------------------------------------|-----------------------------------------------------------------------------------------|----------------------------------------------------------------------------------------------------------------------|
| ANC 1000-1199
Platelets 75-99 K                                                                                                            | Hold therapy until ANC at least 1200 and Platelets at least 100,000                     | If resolution in 1 week, continue same dose *
If resolution > 1 week, then dose reduce 1 level                    |
| Grade 3 Neutropenia
Grade 2 - 4 Thrombocytopenia                                                                                           | Hold therapy until ANC at least 1200 and Platelets at least 100,000                     | Once resolution to ANC at least 1200 and Platelets at least 100,000, dose reduce 1 level for subsequent treatments * |
| Febrile neutropenia
Grade 4 Neutropenia
(at any time during therapy)                                                                    | Hold therapy until resolution of acute episode and above hematological requirements met | Dose reduce 1 level for subsequent treatments *                                                                      |

\* May consider growth factor support for subsequent treatments.

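### Section 7 limits its hold and reduction rules to DLTs or to the time after the DLT window, while Sections 7.1.4, 7.1.5, 7.2.4 and 7.3 order holds for non-DLT toxicity without that limit

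*Protocol*

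**What the plan says.** The opening of Protocol Section 7 gives two instructions for the DLT window. The first is "Patients should remain on the assigned doses of therapy throughout the period of assessment of DLTs", with exceptions only for an observed DLT and for withdrawal. The second fixes the reach of everything that follows: "The following guidelines for dosing delay and/or dose modifications apply to patients who either experience a DLT during the first 28 days (dose level 1", continuing to the 35-day window of levels 2-4, "OR develop treatment-related toxicities after that period of assessment". It names delays as well as dose changes, so it covers holds and reductions alike.

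Several DLTs in Sections 3.2 and 7 carry a severity or duration condition. Examples are "grade IV hematological toxicity > 7 days" and "grade III diarrhea leading to hospitalization or lasting > 48 hours despite aggressive anti-diarrheal medication". Most other grade 3 nonhematological toxicity must last more than a week.

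The subsections set lower triggers and do not mention the window:
- Section 7.3.2, low counts on the irinotecan day: "Hold therapy until ANC at least 1200 and Platelets at least 100,000". Its row for febrile or grade 4 neutropenia is marked as applying throughout therapy, not only on dosing days.
- Section 7.3.4 (the number is used twice, for late diarrhea and for nausea/emesis): irinotecan is held, with both tables starting at grade 2.
- Sections 7.1.4, 7.1.5 and 7.2.4 (dermatologic): grade 3 rash or grade 3 diarrhea leads to a hold when it appears.
- Section 7.1.3: "If QTc prolongation is confirmed, ZD6474 should be withheld".

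The Alert Page clarification on potassium adds that, as for other toxicities, the threshold for holding is grade 3. It attaches no DLT or window condition.

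**The concern.** A patient with toxicity inside the window that falls short of a DLT comes under two incompatible orders. The opening of Section 7 says to continue at the assigned dose and that the delay and modification guidelines do not yet apply. The guidelines themselves say to hold, and in some rows to reduce.

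Two things are at stake. One is safety: the protocol does not tell the treating clinician which order to follow for toxicity it elsewhere treats as a reason to hold. The other is the primary endpoint. The MTD rests on DLT counts in cohorts of three, and the document states no minimum exposure for counting a patient as DLT-free. If a dose is held, a patient can be counted as free of DLT at a dose not fully received. The protocol expects three centers, and its text does not secure that all of them resolve the conflict in the same way.

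**Working it through.** **1. The passages side by side.** For each event the opening of Section 7 gives the same answer: not a DLT, so stay on the assigned dose.

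| Event inside the window | Why it is not a DLT (3.2, 7) | What the subsection orders |
|---|---|---|
| ANC 1000-1199 or platelets 75-99 K on the irinotecan day | Below grade 4 | 7.3.2: hold; reduce one level if recovery takes over a week |
| Grade 3 neutropenia without fever on the irinotecan day | Below grade 4 | 7.3.2: hold, then reduce one level |
| Grade 4 neutropenia without fever, 7 days or less | Too short | 7.3.2: hold and reduce one level, whenever it occurs |
| Grade 2 late diarrhea; grade 2 nausea or vomiting | Never a DLT at grade 2 | 7.3.4: hold; reduce one level if supportive therapy was already optimal |
| Grade 3 diarrhea, 48 hours or less, no hospitalization | Too short | 7.1.5: withhold ZD6474; 7.3.4: hold irinotecan (late diarrhea, levels 2-4) |
| Grade 3 rash, one week or less | Too short | 7.1.4: withhold and reduce ZD6474; 7.2.4: hold cetuximab |

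Level 1 has no irinotecan, so there only the 7.1 and 7.2 conflicts apply.

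**2. Timing.** For the DLTs that need more than 48 hours, more than 7 days or more than a week, the event is not yet a DLT when the decision to hold falls due. Letting the opening of Section 7 govern therefore means dosing on until the duration is met, whereas the subsections act when the event is detected.

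**3. Irinotecan in the window.** Inputs: start on day 15 (Section 3.1), every other week (Section 5.1), window of 35 days (Sections 3.2 and 7).
- Planned days: 15, 15 + 14 = 29, 29 + 14 = 43. Two fall within 35 days: 15 and 29.
- One-week hold at the second dose: 29 + 7 = 36, which is after day 35.
- Doses received in the window: 1 of 2, or 50%.

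**4. ZD6474, outer limit.** Section 7.1 allows a hold of up to 3 weeks (21 days). If all of it fell in the window, the dosing days left would be (28 - 21)/28 = 25% at level 1 and (35 - 21)/35 = 40% at levels 2-4. These are extremes, not expectations.

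**5. The design figures that depend on the DLT count.** From the Section 3.1 rule, P(too toxic) = 1 - [(1-p)^3 + 3p(1-p)^2 x (1-p)^3]. At p = 20, 30, 40, 50 and 60% this gives 0.2914, 0.5057, 0.6907, 0.8281 and 0.9176. Section 13 states 0.29, 0.51, 0.69, 0.83 and 0.92. The table reproduces and is not disputed; it assumes one DLT rate per dose level.

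**6. Illustration only.** Suppose a share h of patients is held for non-DLT toxicity and their DLT risk falls to r times the full-dose risk, so the effective rate is p(1-h) + p x r x h. Neither h nor r is in the protocol. With p = 40%:
- h = 10%, r = 0.75: effective rate 39%, P(too toxic) 0.67.
- h = 40%, r = 0.5: effective rate 32%, P(too toxic) 0.55.

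The full-dose value is 0.69. This shows the direction under assumed inputs and does not estimate what happened in the trial.

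**The case against.** The best reply is that a chapter's opening scope statement governs its subsections, which need not repeat it. On that reading silence in Sections 7.1.4 and 7.1.5 is no contradiction, and patients who stay DLT-free also stay on assigned doses, so exposure is comparable. This does not hold throughout. The 7.3.2 row for febrile or grade 4 neutropenia says it applies throughout therapy. That phrase may have been meant to contrast with counts on the dosing day, but its range still includes the window. The Alert Page clarification sets the threshold for holding at grade 3 without a DLT condition. Section 3.1 also foresees drugs being held within a cycle and does not except cycle 1.

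A second reply is that Section 7 excepts withdrawn patients and Section 11 lets the investigator remove a patient when continuing is unsafe. That is true, so nobody is bound to full dosing regardless of toxicity. Removal is not a hold, however, and does not settle which instruction applies.

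Three limits stand:
- A reader might infer that the QTc hold rules are switched off when events are most frequent, since Section 6.1 says of the 12 confirmed prolongations in the cited monotherapy study: "Of these, 6 occurred in the first 28 days, and 2 in the following 28 days". The documents do not support this. Grade 3 or greater cardiac toxicity is itself a DLT with no duration condition, and the protocol does not map its QTc limits to grades. Some 7.1.3 holds may be caught in the conflict, but which ones cannot be settled. The 6 of 12 describes timing in another study and does not measure this defect.
- Apart from grade 4 or febrile neutropenia, 7.3.2 acts on counts on the day of the scheduled dose. Grade 3 neutropenia that has recovered by day 29 triggers no hold.
- Definitions of who is evaluable for DLT are often left to the SAP, which is not at hand.

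**Conclusion.** The contradiction is in the text and does not depend on any assumption. Inside the DLT window the opening of Section 7 and the subsections give opposite orders for several non-DLT toxicities, most plainly under Section 7.3 on day 29 at levels 2-4. It should be corrected, because it bears on patient safety and on the count that determines the MTD.

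Its measurable size is limited. If irinotecan is held for one week, a patient can count as DLT-free after one of two planned doses. That rests on the two-week schedule being kept up to day 29 and on the hold rule being followed.

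A reader might go further and infer that exposure in DLT-free patients was in fact not comparable, or that escalation was biased. The protocol does not show that. It gives no frequency of in-window holds and no evidence that centers acted differently, so any effect on escalation is unknown. No view is taken on which clinical rule should prevail.

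**What to change.** Reconcile the two scope sentences at the head of Section 7 with Sections 7.1 to 7.3 and with the Alert Page clarification, so that a single instruction applies inside the DLT window. The clinical team decides which. The same revision should say which QTc events under 7.1.3 count as cardiac DLTs, so that the reach of the rule there is clear.

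Report in-window holds and reductions, by drug and dose level, beside each cohort's DLT count, so that a reader can see how many DLT-free patients received the planned doses. A rule on how such patients enter the cohort count, such as a minimum exposure with replacement, would be a useful addition, but it is optional and could sit in the SAP.

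The cost is a wording amendment and one table or listing from dosing data that Section 8.3.3 already has recorded in the case report form. Since the front pages show accrual closed in May 2010, the reporting part now has most of the practical value.
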